### Objectives {7}

The primary objective is to compare the effect of systemic corticosteroids versus placebo on the number of ventilator-free days during the 28 days after randomization in patients with COPD admitted to an ICU, a step-up unit, or a respiratory care unit for a severe acute exacerbation requiring mechanical ventilation (invasive and/or NIV).

The secondary objectives are to compare the effect of systemic corticosteroids versus placebo on:The rates of NIV failure (defined as the need for intubation within the 7 days following randomization)The duration of mechanical ventilation (invasive and NIV)Circulatory support (use of vasopressor) within 28 days of randomizationLengths of stay in the ICU/step-down unit/respiratory care unit and in the hospitalDyspnoea and comfort (patient-reported outcome) at randomization, ICU discharge, and day 90ICU, in-hospital, and day 28 and day 90 mortalities, as well as the standardized mortality ratioThe proportion of new exacerbations/hospital admissions between hospital discharge and day 90The proportion of patients with adverse events related to corticosteroids (including severe hyperglycaemia during the first 5 days after randomization, gastrointestinal bleeding, uncontrolled arterial hypertension, ICU-acquired weakness, ICU-acquired infections, and delirium).

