**Fig. 1 Fig1:**
[figure not shown]
Study design. COPD: chronic obstructive pulmonary disease; ICU: intensive care unit; VFD-28: ventilator-free days and alive at day 28

**Table 1 Tab1:** Schedule of assessments and procedures

	**Day 0**	**Daily (days 1–27)**	**Day 28 or ICU discharge**	**Day 90**^**a**^
Inclusion and exclusion criteria	X			
Informed consent	X			
Randomization (between day 0 and day 1)	X			
Demographic data and comorbidities	X			
Clinical data	X	X	X	
Laboratory data (as appropriate)	X	X	X	
Eosinophilic polynuclear cell count in blood (before 1st dose of protocol treatment) if data available	X			
Radiological data (within 24 h)	X			
Microbiological data (within 48 h)	X			
SAPS II	X			
SOFA (if data available)	X	Days 3, 7, 14, 21	X	
RASS (if invasive mechanical ventilation)	X	X	X	
Mechanical ventilation	X	X	X	
NIV (duration/day, IP, PEEP, FiO_2_)	X	X	X	
Invasive MV (mode, IP or RR × tidal volume, PEEP, FiO_2_)	X	X	X	
Sedative drugs	X	X	X	
Neuromuscular blockers	X	X	X	
Catecholamine infusion	X	X	X	
Adverse event potentially related to corticosteroids and/or changing study drug		X	X	
Serious adverse event^b^	X	X	X^b^	X^c^
ICU length of stay		X	X	X
Hospital length of stay		X	X	X
Number of new exacerbation(s)/hospitalization(s) since hospital discharge				X
Dyspnoea, comfort (patient-reported outcome)	X		X	X
Vital status		X	X	X

*SAPS II* Simplified Acute Physiology Score II, *SOFA* Sepsis Organ Failure Assessment, *RASS* Richmond Agitation-Sedation scale, *NIV* Non-invasive ventilation, *IP* Inspiratory pressure, *PEEP* Positive end-expiratory pressure, *FiO*_*2*_ Fraction of inspired oxygen, *MV* Mechanical ventilation, *RR* Respiratory rate, *ICU* Intensive care unit

^a^Telephone call

^b^Serious adverse events will be collected for 20 days after the last experimental treatment injection

^c^Only if the serious adverse event is related to the study medication

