#### Secondary outcome measures

NIV failure rate, defined as the need for intubation within the 7 days following randomizationThe duration of invasive mechanical ventilationThe total duration of mechanical ventilation (including invasive and NIV)Vasopressor-free days and alive at day 28Length of stay in the ICU, the step-down unit, and the respiratory care unitIn-hospital length of stayDyspnoea and comfort (patient-reported outcome) at inclusion, ICU discharge, and day 90 assessed using the dyspnoea analogue scale: “How much is the intensity of the worst breathing difficulty you have experienced in the last 24 h” from 0 (none) to 10 (extremely); “How much anxiety/distress has the breathing difficulty caused you in the last 24 h” from 0 (none) to 10 (extremely)Dyspnoea and comfort (patient-reported outcome) with standardized questionnaires at day 90: COPD assessment test and the Dyspnoea-12 questionnaireNumber of new exacerbation(s)/hospitalization(s) between hospital discharge and day 90ICU, in-hospital, day-28, and day-90 mortalitiesStandardized mortality ratioNumber of severe hyperglycaemias requiring intravenous insulin therapy during the first 5 daysNumber of gastrointestinal bleeding(s), defined as an acute loss of 2 g/dL of haemoglobin requiring a red blood cell transfusion or gastroscopic evaluationNumber of uncontrolled arterial hypertension(s): unusual hypertension requiring the introduction or addition of an antihypertensive medication compared to usual medicationsICU-acquired weakness (Medical Research Council [MRC] score < 48/60) assessed on day 28 or at the time of ICU dischargeNumber of ICU-acquired infections: bacteraemia of any cause, catheter-related infection, hospital-acquired pneumonia (non-intubated patients), ventilator-associated event (intubated patients), probable or possible ventilator-associated pneumoniaDelirium during the ICU stay.

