## Statistical methods

### Statistical methods for primary and secondary outcomes {20a}

All analyses will be performed by the study statistician according to a predefined statistical analysis plan, using the latest versions of R software© (R Foundation for Statistical Computing, Vienna, Austria) or Statistical Analysis System© (SAS). A two-tailed *p* value of less than 0.05 will be considered as indicating statistical significance.

In accordance with the CONsolidated Standards Of Reporting Trials (CONSORT) statement, a flow diagram will describe the progress of patients in the two groups through the phases of the trial (enrolment, intervention allocation, intervention received, follow-up and data analysis). The analysis will be performed on an intention-to-treat basis. In case of premature stop or withdrawal from the study, patients will not be substituted. Missing values will be described and, according to nature and frequency, multiple imputation methods will be used. A per-protocol analysis will be used as a sensitivity analysis, excluding patients who were wrongly randomized or did not receive the allocated intervention. Comparative analysis will systematically be done with (main analysis) and without adjustment on randomization stratification factors.

Quantitative data will be described as means, medians, standard deviations, and interquartile ranges. Nominal data will be described as percentages with 95% confidence intervals. Proportions of missing data will be given. Patient characteristics will be described by centre and compared. Quantitative data will be compared using *t*-tests or non-parametric tests (Mann–Whitney sum rank) when the distribution does not approach symmetry even after suitable transformation (Tukey’s ladder of powers). Qualitative data will be compared by means of chi-square tests or Fisher exact tests. Time-to-event data (survival) will be described using Kaplan–Meier curves.

The analysis of the primary outcome (i.e., distribution of VFDs that is highly skewed) will be performed by a multivariate non-parametric test, taking into account stratification and minimization criteria used in the randomization [21]. The final test will be performed at a 0.049 two-sided alpha risk to guarantee a global 5% alpha level.

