The main analysis will be performed according to the intention-to-treat principle on the full dataset, while analyses on imputed data dealing with missingness will be considered as sensitivity analyses. As a secondary analysis, a time-to-event model, where death and becoming ventilator free are competing risks, with a fixed factor corresponding to the randomization arm, centre being considered as a random factor, taking into account other prognostic factors and their interactions with the randomized treatment, will be developed.

The analysis of the effect of the intervention on secondary criteria: mortality, adverse events, and length of ventilation, will be performed using generalized linear model regression. The link function and distribution of errors will be chosen according to the nature of the response: logistic and binomial if the response is binary (mortality), identity and Gaussian if the response is considered continuous. Time-to-event censored data (becoming ventilation free or death being competing risks) will be analysed by piecewise exponential regression models. The main secondary analyses will firstly be stratified on randomization criteria without further adjustment then, after bivariate screening, the main confounders (*p* value < 0.2 or retrieved from the literature) and interactions with treatment will be tested in a multivariable model. The shape of the relationship of continuous factors will be explored by fractional polynomials. Goodness-of-fit will be verified (influential observations, R2, discrimination, calibration) and performance of the models will be assessed by Akaike information criteria.

These analyses will be performed on the intention-to-treat groups, except for safety or tolerability criteria, which will be analysed on per-protocol populations.

Analyses will be performed in the NIV or invasive ventilation subgroup (prespecified in the analysis plan) to assess the homogeneity of the difference between the two treatment groups. These subgroup analyses will be supplemented by interaction tests between the treatment and the subgroup variables using Breslow & Day tests. The results will be graphically presented using Forest plots.

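### The pre-treatment dyspnoea and distress scores are listed as compared outcomes but left out, as covariates, of the main analysis of their own follow-up

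*Protocol article*

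**What the plan says.** **Collection.** Table 1 of the protocol article schedules patient-reported dyspnoea and comfort on Day 0, at day 28 or ICU discharge, and at day 90. Secondary outcome measures describes two items scored 0 to 10: the intensity of the worst breathing difficulty, and "How much anxiety/distress has the breathing difficulty caused you in the last 24 h".

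**Outcome list.** Objectives {7} introduces the secondary objectives as being to "compare the effect of systemic corticosteroids versus placebo on" a list of items. One item is dyspnoea and comfort at three times, the first being randomization. Secondary outcome measures repeats the three times and calls the first one inclusion.

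**Adjustment, general rule.** Statistical methods {20a} states: "Comparative analysis will systematically be done with (main analysis) and without adjustment on randomization stratification factors". Sequence generation {16a} gives those factors as initial ventilation type, pneumonia, and corticosteroids in the last 48 h.

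**Adjustment, secondary criteria.** A later paragraph of {20a} covers "secondary criteria: mortality, adverse events, and length of ventilation, will be performed using generalized linear model regression". It continues: "The main secondary analyses will firstly be stratified on randomization criteria without further adjustment". A second step follows once candidate covariates have been examined one at a time. There, according to the same sentence of the protocol: "the main confounders (*p* value < 0.2 or retrieved from the literature) and interactions with treatment will be tested in a multivariable model".

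**Tests for quantitative data.** The general paragraph of {20a} offers t-tests, "or non-parametric tests (Mann–Whitney sum rank) when the distribution does not approach symmetry". It does not link these tests to the dyspnoea scales.

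**The concern.** Two things look wrong.

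First, a score taken at randomization precedes the study drug. A between-arm comparison of it can show only chance imbalance, so it does not belong in a list of effects to be compared.

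Second, the baseline value of a scale is the natural covariate for the same scale at follow-up. The trial collects it, but the main form of comparison adjusts for three factors that do not measure dyspnoea. If Day 0 and follow-up scores are correlated, the comparisons at ICU discharge and day 90 carry variance that could have been removed, and any chance imbalance at Day 0 stays in the estimate.

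At stake is the precision of the only patient-reported scales that the trial measures repeatedly. The primary outcome and the sample size are not affected.

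**Working it through.** **1. The plan's own figure.** The article gives no power, standard deviation or target difference for dyspnoea. Its only sample-size figure is for ventilator-free days, and the last step reproduces: 200 × 1.10 = 220 per group, × 2 = 440. Below, 200 per group serves only as an illustration. The proportional gains do not depend on it.

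**2. Is the Day 0 score in the main analysis?** The general rule in {20a} adjusts for the stratification factors. {16a} lists three, none of them a dyspnoea or distress score. So the Day 0 score is not in the main analysis. If the scheme for secondary criteria also applies to dyspnoea, it has two routes into the second step: screening at p < 0.2, or retrieval from the literature. Neither makes it a fixed covariate of the main analysis.

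**3. What leaving it out costs.** Let rho be the correlation between the Day 0 and follow-up scores given the strata. It is assumed, because the documents do not give it.

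- Residual variance after adjustment = (1 − rho²) × unadjusted variance.
- Standard error ratio = √(1 − rho²).
- Power after adjustment = Φ[(1.960 + z of starting power)/√(1 − rho²) − 1.960], two-sided 5%.
- Unadjusted n per group for equal precision = 200/(1 − rho²).

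Example, starting power 80%, rho 0.5: (1.960 + 0.842)/0.866 − 1.960 = 1.275, and Φ(1.275) = 89.9%.

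| rho (assumed) | Variance cut | SE cut | Power, from 80% | Power, from 50% | Equivalent n per group |
|---|---|---|---|---|---|
| 0.2 | 4% | 2.0% | 81.6% | 51.6% | 208 |
| 0.3 | 9% | 4.6% | 83.6% | 53.8% | 220 |
| 0.4 | 16% | 8.3% | 86.4% | 57.1% | 238 |
| 0.5 | 25% | 13.4% | 89.9% | 61.9% | 267 |

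The starting powers of 80% and 50% are illustrations, not figures from the plan. A regression simulation with 200 per arm and three binary strata gave SE ratios of 0.955 at rho 0.3 and 0.868 at rho 0.5, against 0.954 and 0.866 from the formula.

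**4. Allowing for missing Day 0 scores.** Sample size {14} expects 25% of patients to be invasively ventilated. Assume, for illustration, that 25% of patients have no Day 0 score and are kept through a missing-indicator. The variance cut is then about 0.75 × rho².

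| rho (assumed) | Variance cut | Power, from 80% |
|---|---|---|
| 0.2 | 3% | 81.2% |
| 0.3 | 6.75% | 82.7% |
| 0.4 | 12% | 84.8% |
| 0.5 | 18.75% | 87.5% |

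**The case against.** The strongest objection is that the sentence ruling out further adjustment at the first step is not about dyspnoea. Its paragraph names deaths, adverse events and ventilation time. That stands: its reach to dyspnoea is an inference. The point does not depend on it, however, because the general rule is said to apply systematically and leads to the same main analysis.

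A reader might infer that the plan fixes a stratified t-test or Mann–Whitney test for these scales. It does not. Those tests stand in a general paragraph that also covers patient characteristics.

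A reader might also infer that the precision is lost for good, or that the Day 0 score can enter only by passing a p-value screen. The text does not support this either: a multivariable step is planned, and retrieval from the literature is a second route into it.

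It can be said that covariate choice for one secondary outcome belongs in the statistical analysis plan, which is not shown. Silence would indeed be no finding. Here the protocol states what the main analysis adjusts for, and an analysis plan that follows it would leave the Day 0 score out.

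The three time points can also be read as an assessment schedule, and no section specifies a baseline test as an outcome analysis. A baseline difference being reported as a result is therefore only a possibility. Read literally, though, the objective places the randomization score among the effects to be compared.

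Finally, the gain may be small. The Day 0 item asks about the worst breathing difficulty of the last 24 h in patients enrolled for acute respiratory failure, so a narrow range and a weak correlation with day 90 are plausible. That stands.

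**Conclusion.** The point holds as a minor matter of efficiency and wording. The Day 0 score is listed as a compared outcome time point, which it cannot meaningfully be, and it is not a covariate in the main analysis of the same scale at follow-up.

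The residual variance forgone is about rho² among patients with a Day 0 score: 4% to 25% for rho from 0.2 to 0.5. It is less overall if some intubated or encephalopathic patients cannot report. A comparison with 80% power would gain about 2 to 10 percentage points with complete baseline scores, and about 1 to 7 if a quarter were missing. All of this rests on an assumed correlation.

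The text does not support a claim of bias: a randomized comparison adjusted for the strata alone is valid. The COPD assessment test and Dyspnoea-12 are collected only at day 90, so they have no baseline of their own and are outside this point.

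**What to change.** 1. In Objectives {7} and Secondary outcome measures, list the two analogue scales as outcomes at ICU discharge and day 90 only. Report the Day 0 score as a baseline characteristic.
2. In {20a}, or in the analysis plan with a matching change to the general rule, prespecify the main analysis of each scale as ANCOVA, or rank-based ANCOVA if the scores are skewed. The fixed covariates are the Day 0 score of the same scale and the three stratification factors.
3. State a rule for missing Day 0 scores, such as a missing-indicator, so that no patient is dropped for lacking one.

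The cost is wording, since the Day 0 scores are already scheduled. The small downside is having to handle baseline scores that some patients cannot give.

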### Methods in analysis to handle protocol non-adherence and any statistical methods to handle missing data {20c}

The trial will follow the modified intent-to-treat principle as defined above, so we will not exclude data from the database in case of intervention discontinuation. We will follow the participants who discontinue the intervention during the study duration, unless the participant asked not to be followed.

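### Safety outcomes are assigned to the per-protocol population, which removes exposed patients from the harm comparison; a safety set of all treated patients is needed

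*Protocol article*

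**What the plan says.** All references are to the protocol article.

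- **Scope.** Section {20a} counts harms among the secondary criteria to be modelled: "The analysis of the effect of the intervention on secondary criteria: mortality, adverse events, and length of ventilation". It places these analyses on the intention-to-treat groups, "except for safety or tolerability criteria, which will be analysed on per-protocol populations".
- **Definition of per-protocol.** Section {20a} gives one definition: "A per-protocol analysis will be used as a sensitivity analysis, excluding patients who were wrongly randomized or did not receive the allocated intervention". No set of all treated patients is named anywhere.
- **Efficacy set.** Section {20a} states "The analysis will be performed on an intention-to-treat basis" and later "The main analysis will be performed according to the intention-to-treat principle on the full dataset". Section {20c} then states "The trial will follow the modified intent-to-treat principle as defined above", and adds "we will not exclude data from the database in case of intervention discontinuation".
- **Place of harm in the trial.** Objectives {7} lists corticosteroid-related adverse events as a secondary objective, with six named types. The Discussion says that these events will receive particular attention.

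**The concern.** A harm analysis should count events in the people exposed to the drug. The per-protocol set is built to answer a different question, and section {20a} itself treats it as a sensitivity analysis before making it the only set named for safety. Its exclusions are decided after randomisation and can take dosed patients, with their events, out of the comparison.

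The eligibility criteria make this more than a formality. Section {10} excludes uncontrolled diabetes, uncontrolled severe hypertension and bleeding from a gastrointestinal ulcer. The secondary outcomes in {12} count severe hyperglycaemia, uncontrolled hypertension and gastrointestinal bleeding. A patient enrolled in breach of one of these criteria may be prone to the matching harm, and the breach may come to light because the harm occurred. Exclusion and outcome could then be linked.

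The trial aims to inform guidelines on a treatment whose benefit must be weighed against known harms. The safety comparison should therefore not depend on who is judged per-protocol.

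**Working it through.** **1. Who leaves the safety analysis under the text of {20a}**

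| Patient | Exposed to study drug? | In the per-protocol set? | In an all-treated set? |
|---|---|---|---|
| Dosed, later judged wrongly randomised | Yes | No | Yes |
| Given the other arm's product | Yes | No | Yes, under product received |
| Started the allocated product, stopped early | Yes | Open: depends on how receipt is read | Yes |
| Never dosed | No | No | No |

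The first two rows are losses on any reading. The third is conditional: {20a} does not say whether part of the 5-day course counts as receiving the intervention. The condition matters because {22} lets the investigator withdraw treatment, temporarily or permanently, after an adverse event. The fourth row does not separate the two sets.

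**2. What the exclusions could do to a harm comparison**

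The document gives no adverse event rates and no expected number of exclusions, so this step is an illustration under assumptions and not an estimate.

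- Arm size, from Sample size {14}: 200 × 1.10 = 220 per group, 440 in total. This reproduces the plan's figure.
- Assumed: event rates of 20% (steroid) and 10% (placebo), and a fraction f = 5% removed from each arm, leaving 220 × 0.95 = 209.
- Let r be the event rate among the removed steroid patients. The rate in those who remain is (0.20 − f·r) / (1 − f). The placebo rate is held at 10%.
- Power (two-sided 5%) = Φ{[d − 1.96·√(2p̄(1 − p̄)/n)] / √[(p₀(1 − p₀) + p₁(1 − p₁))/n]}, where d = p₁ − p₀ and p̄ is the mean of the two rates.

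| Case | Steroid rate | Difference (points) | Power |
|---|---|---|---|
| No exclusion, n = 220 | 20.0% | 10.0 | 84% |
| r = 20% (unrelated to events) | (0.20 − 0.010)/0.95 = 20.0% | 10.0 | 82% |
| r = 50% | (0.20 − 0.025)/0.95 = 18.4% | 8.4 | about 70% |
| r = 80% | (0.20 − 0.040)/0.95 = 16.8% | 6.8 | about 54% |

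Two further cases show that the direction is not fixed:

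- If the removed steroid patients had no events (r = 0), the rate becomes 0.20/0.95 = 21.1% and the difference rises to 11.1 points.
- If 50% of those removed had the event in both arms, the placebo rate becomes (0.10 − 0.025)/0.95 = 7.9% and the difference is 18.4 − 7.9 = 10.5 points.

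Attenuation therefore needs exclusion to be linked to events more strongly in the steroid arm.

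**3. The efficacy set**

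Section {20a} says intention-to-treat twice, once specifying the full dataset. Section {20c} says modified intention-to-treat and points back to a definition, but the text shown contains none. The one operative rule in {20c} keeps the data of patients who discontinue, which agrees with {20a}. No passage states an exclusion from the primary analysis.

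**The case against.** The strongest reply has three parts.

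- **Early stoppers.** On its plain reading, {20a} removes only patients who were wrongly randomised or did not get the allocated product, and someone who started and stopped did get it. The commitment in {20c} to keep data after discontinuation points the same way. This stands to the extent that loss of early stoppers must be stated as conditional. It does not settle the matter, because {20c} speaks of the database while {20a} names the analysis set.
- **Balance between arms.** The trial is double-blind, with identical containers and computer-assigned kit numbers ({16b}, {17a}), so exclusions need not differ by arm or follow an event. This also stands: the document gives no ground for asserting a bias of known direction or size.
- **Oversight.** Serious adverse events go to the sponsor, apart from a prespecified list, and the safety board is kept informed whatever the analysis set. That protects patients during the trial but does not repair the final comparison.

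None of this restores the two groups of exposed patients who are lost on any reading.

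Three stronger readings are tempting and should not be drawn.

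- A reader might infer that the word *modified* leaves the primary test open to exclusions. The two statements in {20a} and the retention rule in {20c} do not support that.
- A reader might size that risk from the 10% inflation in {14}. That is an allowance for consent withdrawal, and patients who refuse use of their data would be absent after the repair as well.
- A reader might count rescue corticosteroids in placebo patients ({11b}) against the per-protocol set. They dilute the contrast in every analysis set.

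**Conclusion.** The point holds. The protocol fixes the wrong population for its safety and tolerability criteria. This is an explicit choice in the protocol and not a detail left to an analysis plan that is not shown. The certain consequence is that dosed patients judged wrongly randomised, and patients given the other arm's product, leave the harm comparison. Loss of patients whose treatment was stopped for an adverse event is possible but rests on an open reading of the definition.

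The size cannot be derived from the document. The illustration, with assumed rates of 20% and 10% and 5% removed per arm, runs from no shift in the difference when exclusion is unrelated to events to a fall from 10.0 to 6.8 points when 80% of the removed steroid patients had the event and the placebo rate is held at 10%. It shows what could happen and is not evidence of what will.

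The reference in {20c} to a modified principle is a real inconsistency but a secondary one. The sample size, alpha and stated primary analysis are unaffected.

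**What to change.** 1. In {20a}, replace the per-protocol assignment for safety with all randomised patients who received at least one dose of study drug, grouped by treatment received. Repeat the comparison in the intention-to-treat grouping as a check.
2. Keep per-protocol as a sensitivity analysis only, and state whether an incomplete course counts as receiving the allocated intervention.
3. Report by arm the number of patients outside each set, with reasons.
4. In {20c}, delete *modified* so that the section agrees with {20a}, or define the term and list its exclusions, for example refusal at deferred consent ({26a}).

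The cost is a wording change to the protocol and the analysis plan, best made before database lock and unblinding. No new data are needed, and the sample size, alpha and power for the primary outcome do not change.
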